### T4TM intervention

T4TM provides a new daily challenge over six weeks, a time frame selected to provide participants with enough opportunities to form the habit of visiting the T4TM web-application daily [122,123]. Participants log onto T4TM through their cell phones (or a computer), a technological requirement for the study that does not pose an undue burden on participants, especially as low-income households use social networks more frequently than adolescents in higher-income households [71,72]. Participants are encouraged to engage with T4TM as frequently as they like. Frequency of use and number of challenge completion will be logged by the application. Throughout the six-week intervention, participants will receive a daily text message, containing the challenge name and the URL to open the web-application directly through their smartphones. When the participants visit the T4TM page they will see: 1) the name of the challenge, 2) why the challenge is important, 3) tips to complete the challenge, 4) how many people have completed the daily challenge, and 5) a space to leave comments. In addition to the rotating challenges, adolescent mothers can browse T4TM for information about infant feeding, links to related topics, a discussion forum, and a place where they can receive expert advice from a RD or RN. When participants complete a daily challenge, they may click on the “I Did This” button to publicly acknowledge their accomplishment, which serves as a motivational feedback function as they observe other mothers’ completion of the challenges, thereby establishing healthy feeding practices as normative for the young mothers [124]. Participants continue to receive usual MIHP care during the intervention.

### Procedures

Data are obtained by trained data collectors using both self-report questionnaires and anthropometric assessment. To ensure consistency and accuracy of data collection, a half-day intensive training session was held for data collectors prior to the collection of data, to be followed by a booster session in year 2. Training consisted of a standardized training guide and protocol including review of the instruments and measurement of infant recumbent length and weight. Telephone contact and email communication occurs between the project manager and the data collector and/or supervisor to facilitate open communication and fidelity to the protocol.

Intervals for data collection reflect time points (at infant age of 4–8 weeks, 3 months, and 6 months old) that align with both infant feeding recommended milestones and the intervention duration. For example, the third data collection occurs when the infant is 6 months old, when solids foods introduction is recommended.

### Measures

#### Maternal outcomes

**Maternal responsiveness** is defined as sensitivity of the behaviors of a mother to her infant’s cues through expert judgment of what her infant needs [91-95]. These behaviors comprise a relationship skill set promoting mothers’ accurate recognition and response to infants’ feeding cues [96,97]. The Maternal Infant Responsiveness Instrument [125] is used to measure maternal responsiveness to infant cues; the scale is valid [126] and reliable (alpha = .83 and .87) [41,127]. We expect the intervention group to have higher scores than the control group.

**Feeding style** expresses the mother’s beliefs about and approach to guiding her infant’s feeding behaviors [97,98]. It also describes how (style) mothers feed their infants (authoritative, authoritarian, permissive, uninvolved) [99-101]. An adapted version of the Infant Feeding Styles Questionnaire (IFSQ) [128,129] is used to measure feeding beliefs and feeding style behaviors [42,43,97-99,129,130]. The IFSQ was pretested and validated with 150 African American first-time mothers with children ≤ 2 years of age [43]. Reliabilities for subscales range from .75 to.95 [128]. We expect the intervention group to score higher in the authoritative range than the control group.

**Feeding practices** are maternal behaviors relating to what is fed, where, how, and how often; they are essential for ensuring healthy eating habits throughout childhood [98,102-104]. The Infant Feeding Index (IFI) [131-134] identifies age-appropriate beverages and foods offered to the infant [135-138] and the appropriateness of feeding environment (i.e., support infant’s self-regulation) per AAP recommendations is a valid measure [131,133,135,136,139]. Of primary concern is the time at which solid foods are first introduced into the infant’s diet. We expect a longer average delay of introduction to solid foods that is closer to the AAP recommendation in the intervention group compared to the control group.

#### Infant outcome

**Infant growth** is the measurement of an infant’s weight and length plotted over time using *z* scores computed from the measures taken at T1 (baseline),T2, post intervention; and T3. Infant weights and lengths will be standardized as weight-for-age percentiles (WAP) and weight-for-age *z*-scores (WAZ), using WHO Anthro [140]. Relative weight gain (or loss) can then be calculated as the difference between WAZ scores at T3 and T1 [140]. Rate of growth proportional to birth weight and body composition (a weight-for-length index) will also be calculated. We expect a greater proportion of infants in the intervention group: 1a) will fall below the 85th percentile of the WHO growth norms at three and six months; and 1b) z score change <0.67 in weight-for-age WHO norms over time periods one-to-three months, and three-to-six months.

The infant’s weight and length is measured at all three time points to provide an objective measure of weight status. The infant is weighed in a clean diaper on an electronic scale and weighed to the nearest half ounce. Infant length is measured in the recumbent position. Digital scales are calibrated prior to weights being taken. These data will be entered into EpiInfo V3.4.3 to calculate weight-for-length z scores.

### Maternal and infant conditions that may influence outcomes

Maternal behaviors affect infant growth over time [102-119] and are the focus within the maternal-infant feeding interaction. Several background factors also affect infant growth [141,142], such as maternal knowledge [143], self-efficacy [144], and infant temperament. The Maternal Knowledge and Self-Efficacy scale [64], a 13-item knowledge scale and 7-item, 6-point Likert self-efficacy scale of dis/agreement, has been used with lower-income mothers of infants (alpha = .72 to .75) [64]. The standardized Pictorial Assessment of Temperament (PAT) [145], a 10-item tool that requires mothers to select how they would categorize their infants’ reaction to everyday situations as represented by drawings, is used for this study. The PAT provides a mean score ranging from 1 to 3 [145], and demonstrates convergent validity with other infant temperament questionnaires [146]. Demographic information is collected via a self-report questionnaire, including age, race, and maternal health.

### Feasibility variables

Feasibility is assessed by rates of enrollment (percent of eligible and approached adolescents), the percentages of daily challenges completed overall, and by individual participants. These data are monitored by project staff through website tracking protocols. Attrition dates and reasons are tracked on all participants enrolled in the study by the project manager. Acceptability and satisfaction are measured at time 2 data collection using a questionnaire developed by the research team that allows participants to rate the utility of the T4TM challenges and content, and give their opinions about the format, ease of use, and delivery method [64].

### Sample size and power calculations

Using non-intervention levels of infant growth to determine sample size, a power analysis using a time-averaged difference (TAD) method [147] indicated a sample size of 80 participants (40 per group) would be necessary to achieve power at .80, with a one-tailed TAD p < 0.05 over three measures and assuming a compound symmetry covariance structure with p = 0.20. A sample of 80 is deemed adequate; it is higher than the often recommended 12 per group [148]. The primary foci of this study include assessment of: 1) the effect size of the intervention to power a larger study, 2) feasibility, 3) practicality of data collection procedures, 4) measurement adequacy, and 5) the ability to implement.

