### Aims and hypotheses

The aim of this study is to compare the effect of a social media intervention for low-income adolescent, first-time mothers of infants 2 months of age or younger, versus standard care on infant weight, maternal responsiveness, and feeding style and practices. Adolescent mothers with infants 2 months of age or younger will be assigned randomly to a control/usual care or intervention condition.

The usual Maternal Infant Health Program (MIHP) care only condition consists of voluntary home visits (one week postpartum, six weeks, and six months) and on-going as needed visits (up to nine during the infant’s first year of life) provided by a Registered Nurse (RN), Licensed Social Worker (LSW), Registered Dietician (RD), infant mental health specialist and/or paraprofessional. Maternal Infant Health Program interventions are based on participants’ individualized plans of care following in-home screening assessments. Content includes a flexible plan of care with visits based on identified domains for both the mother (e.g., family planning, transportation, housing, and breastfeeding support), and the infant (e.g., monitoring infant growth). For the T4TM plus usual MIHP care condition, participants get the same usual care treatment as the control group and also receive text messages for six weeks, reminding them to view the T4TM web-application and complete the behavioral challenges. Daily challenges cycle through a pre-determined schedule and focus on: 1) maternal-infant feeding interaction (maternal responsiveness, infant temperament, feeding style); and 2) feeding practices (e.g., delay of early introduction to solids; how much to feed babies) including the feeding environment (e.g., communication with baby, sitting down to eat, turning off the television). Participants also have the option to retroactively complete challenges posted in the last week. We hypothesize:

H1: The T4TM plus MIHP (intervention group) as compared to the MIHP only (control group) will exhibit a greater proportion of infants: a) with a growth in weight that falls below the 85th percentile of the WHO (World Health Organization) growth norms at three and six months, and b) that have a z-score change <0.67 in weight-for-age WHO norms over time periods one to three months, and three to six months [27,88].

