### Data analysis

Outcomes (infant growth, MR, FS, FP) and maternal and infant factors at baseline (self-efficacy, knowledge, infant age, temperament, type of feeding) will be compared across intervention and control groups using t-test for continuous variables and chi-square test for categorical variables [149,150]. If differences are observed, the relevant variables will be treated as covariates in our post-experiment analyses [149,151,152]. All analyses will use the intention-to-treat [153] principle based on imputed data. The hypothesis regarding differences in outcomes at each follow-up T2 and T3 between intervention and control groups will be tested using the generalized estimating equation (GEE) model [154] for proportional group differences in growth over time. To explore efficacy of the intervention as assessed by MR, FS, FP, evaluated pre-intervention (T1), immediately post intervention (T2), and when the infant is six months old (T3). Both general linear mixed models (GLMM) [155,156], for continuous outcomes and the GEE model for logistic or Poisson regression for binary/ordinal and count outcomes will be considered.

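### The stated power of 0.80 counts the pre-intervention baseline as one of three outcome measures; for the average of the two follow-ups it is about 0.71 at 40 per group

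*Protocol article*

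**What the plan says.** The protocol article sizes the trial on infant growth with a time-averaged difference (TAD) method. Under Sample size and power calculations, the claim is that 40 per group "would be necessary to achieve power at .80". The test and the correlation behind that claim are given in the same sentence: "with a one-tailed TAD p < 0.05 over three measures and assuming a compound symmetry covariance structure with p = 0.20". No effect size, standard deviation or event rate is printed.

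Overall study design lists three data collections: T1 at 4–8 weeks of age, T2 at 10–12 weeks and T3 at 6 months. It sets 40 per group as the number to be retained by T3. The Measures section labels T1 as baseline for infant growth, and Data analysis, speaking of the maternal outcomes, has them "evaluated pre-intervention (T1), immediately post intervention (T2" and T3 at six months.

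H1a, under Aims and hypotheses, concerns infants "below the 85th percentile of the WHO (World Health Organization) growth norms at three and six months". Data analysis says the hypothesis concerns "differences in outcomes at each follow-up T2 and T3 between intervention and control groups" and will be tested with a GEE model.

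**The concern.** A TAD calculation assumes the same group difference at every occasion that is averaged, and it gains precision with each added occasion. With only T1, T2 and T3 available, the three measures must include T1. Under randomisation the expected group difference at T1 is zero, and no hypothesis is tested there. The calculation therefore describes a design with three post-baseline measures, and this trial has two.

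At stake is how the result is read. A reader told that power is 0.80 expects a true effect of the planned size to be missed one time in five. If the real figure is nearer 0.7, a null result on infant growth deserves less weight than the article suggests.

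**Working it through.** **Inputs**, all from Sample size and power calculations: n = 40 per group; power 0.80 (z = 0.842); one-sided alpha 0.05 (z = 1.645); m = 3 measures; compound symmetry with correlation 0.20. The article prints this last value as p; beside a covariance structure it is read here as the correlation ρ.

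**Formula.** For a TAD with unit standard deviation per measure,

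n per group = 2(z_α + z_β)² × V(m) / d², with V(m) = [1 + (m − 1)ρ] / m.

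**Variance factors at ρ = 0.20.**
- V(3) = 1.4/3 = 0.467
- V(2) = 1.2/2 = 0.600
- V(1) = 1.000

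**The plan's own figure.** Without a printed effect size, n = 40 cannot be reproduced independently. Taking the stated 0.80 as exact, the implied standardised effect is d = (1.645 + 0.842) × √(2 × 0.467/40) = 0.380. With m = 3 this returns 40 per group and power 0.80 by construction.

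**Other contrasts at the same effect.** Power = Φ(2.4865 × √(V(3)/V) − 1.645). The effect size cancels, so these results need only the stated power, alpha, m and ρ.
- Average of T2 and T3: Φ(2.4865 × √(0.467/0.600) − 1.645) = Φ(0.548) = 0.708. For 0.80: 40 × 0.600/0.467 = 51.4, so 52 per group (104 in total).
- One follow-up tested alone: Φ(2.4865 × √0.467 − 1.645) = Φ(0.054) = 0.521. For 0.80: 40/0.467 = 85.7, so 86 per group (172 in total).
- All three occasions averaged, with no effect at T1: the mean effect is 2/3 of d, giving Φ(2.4865 × 2/3 − 1.645) = Φ(0.013) = 0.505.

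**Form of the test.** A t-based calculation gives 0.708 and 0.521 for the two-visit average and the single visit. A binary-outcome version with assumed control proportions from 0.40 to 0.75 gives 0.707 and 0.518. The result does not depend on treating growth as continuous.

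**T1 as a covariate.** The variance factor for the two-visit average becomes V(2) − ρ² = 0.600 − 0.040 = 0.560, and power is Φ(2.4865 × √(0.467/0.560) − 1.645) = 0.734. For one visit the factor is 0.960 and power is 0.535.

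**All 100 anticipated participants with complete data (50 per group).** Two-visit average: Φ(2.4865 × √(1.25 × 0.467/0.600) − 1.645) = Φ(0.807) = 0.79.

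**The case against.** Four points on the other side have weight.

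- **The test may itself be an average.** The sentence that refers to each follow-up goes on to a single GEE model of group differences in growth over time. A common group effect in that model is a time-averaged difference over T2 and T3, with power 0.71. A reader might infer that the trial's power is simply 0.52. The wording does not settle that; 0.52 applies only to separate tests at each visit.

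- **More than 40 per group will be enrolled.** The Abstract anticipates 100, and analyses are intention-to-treat on imputed data. Mothers lost between T2 and T3 still contribute T2. This moves the two-visit average towards 0.79, or 0.81 if T1 is also a covariate. These are upper bounds: imputation does not restore lost information, and 40 per group is the article's own retention goal and the number behind its power claim.

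- **The correlation may not be 0.20.** The consequence of a higher value depends on convention. Re-solving the effect so that three measures still give 0.80, the two-visit average has 0.758 at an assumed correlation of 0.5 and 0.787 at 0.8. Holding 0.38 SD fixed, it has 0.62 and 0.56 unadjusted, but 0.78 and 0.95 with T1 as a covariate. With no effect size stated, none of these is established. Data analysis uses covariates only if baseline differences are observed, so the gain from adjustment is not assured.

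- **The trial has pilot aims.** The sample size section lists effect-size estimation and feasibility among its primary foci. That lowers the seriousness, but the 0.80 is still asserted for the growth comparison.

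Two further inferences are not supported. The two H1b change periods share the T2 weight, so positive compound symmetry may not describe them; but a negative correlation would raise the power of their average at a given standardised effect, so this shows no loss. Two-sided power would be lower, but H1 is directional and the article declares a one-tailed test, so the one-sided choice is not an error here.

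**Conclusion.** The stated power does not match the design. Three measures can only be T1, T2 and T3, and T1 precedes the intervention. At 40 per group, power for the T2/T3 average is about 0.71 rather than 0.80, so a true effect of the implied size would be missed about 29% of the time instead of 20%. Averaging T1 in with no effect gives about 0.51.

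These figures assume that the printed p is the correlation, that the stated 0.80 at 40 per group is exact (implied effect about 0.38 SD), and that the effect is equal at T2 and T3. They show that the power statement is wrong as written; they do not show that the trial is unsound or that its power must fall short under every correlation and adjustment. Given its feasibility and effect-size aims, this is a should-fix point.

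**What to change.** In Sample size and power calculations, restate power at 40 per group for two post-baseline measures, and print the assumed effect size and correlation (labelled as such). In Data analysis, say which contrast the GEE will test, the T2/T3 average or a single visit, and quote the power for that contrast: on the present inputs about 0.71 or about 0.52.

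Optionally, pre-specify the T1 value as a covariate instead of leaving it to observed baseline differences. At correlation 0.20 this gives about 0.73 for the average. With the effect held fixed, the variance factor (1 + ρ)/2 − ρ² is again 0.56 at ρ = 0.3 and falls beyond it, so the gain grows at higher correlations.

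No extra participants or visits are needed. The cost is a rewritten paragraph and a less favourable stated power.

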### Data analysis

Outcomes (infant growth, MR, FS, FP) and maternal and infant factors at baseline (self-efficacy, knowledge, infant age, temperament, type of feeding) will be compared across intervention and control groups using t-test for continuous variables and chi-square test for categorical variables [149,150]. If differences are observed, the relevant variables will be treated as covariates in our post-experiment analyses [149,151,152]. All analyses will use the intention-to-treat [153] principle based on imputed data. The hypothesis regarding differences in outcomes at each follow-up T2 and T3 between intervention and control groups will be tested using the generalized estimating equation (GEE) model [154] for proportional group differences in growth over time. To explore efficacy of the intervention as assessed by MR, FS, FP, evaluated pre-intervention (T1), immediately post intervention (T2), and when the infant is six months old (T3). Both general linear mixed models (GLMM) [155,156], for continuous outcomes and the GEE model for logistic or Poisson regression for binary/ordinal and count outcomes will be considered.

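### Baseline variables, including the baseline outcome, become covariates only if a significance test shows a group difference, so the model is chosen from the data and some precision is lost

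*Protocol article*

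**What the plan says.** The Data analysis section of the protocol article names the variables to be compared between arms: "Outcomes (infant growth, MR, FS, FP) and maternal and infant factors at baseline (self-efficacy, knowledge, infant age, temperament, type of feeding"). The comparison is made "using t-test for continuous variables and chi-square test for categorical variables", with no significance level given. The covariate rule follows: "If differences are observed, the relevant variables will be treated as covariates in our post-experiment analyses". The article states no other covariate rule.

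The growth hypothesis concerns "differences in outcomes at each follow-up T2 and T3 between intervention and control groups will be tested using the generalized estimating equation (GEE) model". The maternal outcomes are "evaluated pre-intervention (T1), immediately post intervention (T2), and when the infant is six months old (T3"), by mixed models or GEE. Under Infant outcome, "The infant’s weight and length is measured at all three time points", so a T1 weight exists for the infants. The Randomization section says that allocation was balanced by the four county sites; county is not named in any analysis model.

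**The concern.** Adjustment in a randomised trial is worthwhile when a variable predicts the outcome. A test of baseline difference between arms carries no information on that. It selects variables by the size of a chance imbalance, and at 40 per arm a strong predictor with a moderate imbalance will usually pass as not different.

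Three things are at stake:

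- **Precision.** The T1 value of an outcome may be its best predictor, and the rule would usually leave it out.
- **Interpretation given the data seen.** A moderate, non-significant imbalance in the T1 outcome stays uncorrected in the treatment comparison.
- **A fixed model.** The covariate set is known only after the data are seen. In a logistic model, a different covariate set also changes the odds ratio being estimated.

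This is a stated rule that is badly chosen, not a detail left to an analysis plan. A plan that prespecified covariates would contradict it.

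**Working it through.** **Inputs.** From Sample size and power calculations: "a sample size of 80 participants (40 per group) would be necessary to achieve power at .80"; the test there is one-sided at 0.05 and averages three repeated measurements, and the compound-symmetry correlation is 0.20 (printed as p). Nine variables come from the Data analysis list: infant growth, MR, FS, FP, self-efficacy, knowledge, infant age, temperament and type of feeding, each counted once. Assumptions: baseline tests at two-sided 5%; correlations of 0.5 and 0.7 to show the range.

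**The plan's own figure.** The article gives no effect size or SD, so 40 per arm can only be inverted. For a time-averaged difference over m measures, n per arm = 2(z_α + z_β)² × [(1 + (m − 1)ρ)/m] / d². With z_α = 1.645, z_β = 0.842, m = 3 and ρ = 0.20, the bracket is 1.4/3 = 0.467, and d = 2.487 × √(2 × 0.467/40) = 0.38 SD. The point does not depend on this value.

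**How often the rule selects.** A given T1 variable is selected about 5% of the time (4.9 to 5.1% in simulation) and so omitted about 95% of the time. At least one of nine enters with probability 1 − 0.95⁹ = 0.37 if they are independent.

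**Power, continuous outcome, mean of T2 and T3.** The variance is (1 + ρ)/2 unadjusted and (1 + ρ)/2 − ρ² with the T1 value as covariate. The effect is set to give 80% power unadjusted. The simulation used 40,000 trials per setting.

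| ρ | Variance unadjusted / adjusted | Analytic power, always adjusting | Simulated power: stated rule / always adjusting | n per arm for 80% if adjusted |
|---|---|---|---|---|
| 0.2 (protocol) | 0.60 / 0.56 | 0.824 | 0.796 / 0.816 | 38 |
| 0.5 (assumed) | 0.75 / 0.50 | 0.919 | 0.810 / 0.913 | 27 |
| 0.7 (assumed) | 0.85 / 0.36 | 0.985 | 0.816 / 0.983 | 17 |

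The loss is 2, 10 and 17 points. With a single follow-up and d = 0.38 (20,000 trials), the stated rule against always adjusting gives 0.516 / 0.524, 0.521 / 0.612 and 0.522 / 0.749, a loss of about 1, 9 and 23 points.

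**Binary growth endpoints, as an illustration.** Assumptions: 40 per arm, one follow-up, unit-SD z-scores, 0.5 SD shift, logistic model, 6,000 trials. Power under the stated rule / always adjusting at ρ = 0.2, 0.5 and 0.7:

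- Below a fixed cut at +0.5 SD: 0.46 / 0.48, 0.47 / 0.53, 0.47 / 0.59.
- z-score change from T1 below 0.67: 0.33 / 0.41, 0.41 / 0.45, 0.45 / 0.46.

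The direction is the same, but the size depends on the endpoint. For the change endpoint the loss is largest at low correlation.

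**Type I error, continuous outcome, one-sided 5%.**

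| ρ | Overall, stated rule | Given baseline t > 1 favouring the intervention but not significant: stated rule | Same condition: always adjusting |
|---|---|---|---|
| 0.2 | 5.0% | 8.8% | 5.1% |
| 0.5 | 4.4% | 15.3% | 5.1% |
| 0.7 | 3.8% | 18.3% | 4.7% |

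These are for the mean of T2 and T3. With a single follow-up the conditional error under the rule is about 8%, 14% and 18 to 20%.

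**The case against.** The strongest reply concerns size. The only correlation in the article is 0.20, and there the continuous-outcome loss is 1 to 2 points. The larger losses need correlations that the document does not give. That stands, and 0.5 and 0.7 are shown only as a range.

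A reader might infer that the rule inflates the false-positive rate. It does not: overall error is 4 to 5%, slightly conservative at the higher correlations. What is raised is the error conditional on an imbalance that favours the intervention.

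A reader might also infer that baseline is ignored altogether. The documents do not support that. T1 is among the evaluated time points for MR, FS and FP and may enter as a repeated response, and H1b uses earlier weight in its definition. But the article does not state equal baseline means or a baseline contrast, and a change score is not the same as adjustment. For the three-to-six-month change, the starting weight is itself measured after randomisation.

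Further, baseline differences may not be pure chance here, because data collectors learn the arm on arriving for the baseline visit, where consent is also obtained. This is a fair caution about the premise. It does not make a significance test a sound way to choose covariates.

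Finally, the study is partly a feasibility study. But the article lists the effect size for a larger trial among its primary foci, so a less precise estimate from a data-chosen model would carry forward.

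**Conclusion.** The point holds as a badly fixed covariate rule. If the tests are at 5%, the T1 outcome is omitted as a covariate about 95% of the time, and there is about a 37% chance that at least one of nine variables enters by chance (independence assumed).

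The power cost for a continuous outcome is small at the protocol's correlation of 0.20 (1 to 2 points). It becomes material only if the true correlation is higher: about 10 points at 0.5 and 17 or more at 0.7. For the binary H1 endpoints the size differs. Overall type I error is not inflated. Conditional on a non-significant imbalance favouring the intervention, it is about 8% at 0.2 and 14 to 20% at 0.5 to 0.7.

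The point bears mainly on infant weight, MR and FS, since age at introduction of solids has no useful T1 value. The rule should be changed, mainly because the model is not fixed in advance and the remedy is nearly free.

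**What to change.** Delete the test-then-adjust sentence and state in its place:

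- Each outcome model includes the T1 value of that outcome where one exists: T1 weight-for-age z-score for the growth outcomes, T1 score for MR and FS. Where T1 is modelled as a response instead, baseline means are constrained equal between arms.
- County, by which allocation was balanced, is included in every model.
- For age at introduction of solids, only county is used.
- The baseline table is descriptive and does not select covariates.

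The cost is a change of wording in the analysis section. The T1 measurements and the recruitment county are already part of the trial's data, and the sample size need not change.

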H2: The T4TM plus MIHP (intervention group) as compared to the MIHP only (control group) will have: a) higher average maternal responsiveness scores, b) greater probability of using a positive feeding style, and c) greater average delay in introducing solid foods in keeping with AAP guidelines.

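### T1 maternal scores are adjusted for only after a baseline test and, on the natural reading, also modelled as a response; T1 should enter once, by prior rule

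*Protocol article*

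**What the plan says.** All statements are in the protocol article.

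- **Baseline comparison (Data analysis).** The variables compared between arms include the outcomes themselves: "Outcomes (infant growth, MR, FS, FP) and maternal and infant factors at baseline".
- **Covariate rule (Data analysis).** "If differences are observed, the relevant variables will be treated as covariates in our post-experiment analyses". A T1 outcome value can therefore become a covariate, but only when a test flags it.
- **Occasions (Data analysis).** The growth hypothesis concerns follow-up only: "The hypothesis regarding differences in outcomes at each follow-up T2 and T3 between intervention and control groups". For the maternal outcomes, efficacy is explored "as assessed by MR, FS, FP, evaluated pre-intervention (T1), immediately post intervention (T2), and when the infant is six months old (T3", and the text goes straight on to the models.
- **Models (Data analysis).** General linear mixed models for continuous outcomes, and for the others the "GEE model for logistic or Poisson regression for binary/ordinal and count outcomes will be considered". No arm, visit or interaction term is given.
- **Missing data (Data analysis).** "All analyses will use the intention-to-treat [153] principle based on imputed data", so the analysed data are complete.
- **Purpose (Sample size and power calculations).** Estimating the effect size, so that a larger study can be powered, heads the list of primary foci.

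**The concern.** T1 precedes the intervention, so it carries no treatment effect. It can serve as a covariate, or as a response whose mean is held equal in the two arms. Taken together, the covariate rule and the list of occasions let it be an unconstrained response and a covariate at once. The covariate then fails to do its job in one contrast and over-corrects in another. An arm effect averaged over all three visits is also diluted by a visit at which nothing can have happened. Because the effect size is itself a product of this trial, a shift in the estimate matters even where the test is unharmed. Finally, making the adjustment depend on a baseline test leaves the T1 score unused in most trials, although it is always collected.

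**Working it through.** **Inputs.** From the article: 40 per arm, one-sided 0.05, power 0.80, three measures, compound symmetry with correlation 0.20, complete (imputed) data. Assumed, because the article gives none: SD 1, a true effect d equal at T2 and T3, a two-sided 5% baseline test, and other correlations (rho) to show the range.

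**The plan's own figure.** The time-averaged difference formula is n per arm = 2(z_alpha + z_beta)²[1 + (m-1)rho]/(m d²). No effect size is stated, so 40 per arm can be neither reproduced nor refuted. Inverting it gives d = sqrt(2 × 2.486² × 1.4/(3 × 40)) = 0.38 SD, used below for power.

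**How large the imbalance is when the test triggers.** The SE of the T1 difference is sqrt(2/40) = 0.224. Given |z| > 1.96, the mean of |z| is 2 × 0.0584/0.05 = 2.34, so the mean imbalance is about 0.52 SD. This happens in about 5% of trials per outcome.

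**T1 as response and time-constant covariate, arm-by-visit model, continuous score.** Let D be the observed T1 difference. Given D, the expected raw arm difference at T2/T3 is d + rho·D.

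1. *Change from T1.* The covariate term is the same at every visit and cancels. The expected contrast is d + rho·D - D = d - (1-rho)D. With d = 0.50, rho = 0.5 and D = ±0.52 this is 0.24 or 0.76 (simulated 0.24 and 0.75). In 300 simulated trials at each of rho 0.2 and 0.5, the contrast with and without the covariate agreed to within 4e-16. Its slope on D was -0.82 and -0.57 (theory -0.80 and -0.50).
2. *Arm difference at T2/T3.* The slope on T1 is 1 at T1 and rho at T2 and T3. A single common slope is therefore (1+2rho)/3, which is too steep for follow-up. The expected contrast is d + rho·D - D(1+2rho)/3 = d - D(1-rho)/3. At rho 0.5 this is 0.50 ∓ 0.52/6 = 0.41 or 0.59. Simulation gives 0.41/0.58 at rho 0.5, 0.38/0.62 at 0.3 and 0.45/0.56 at 0.7.
3. *T2/T3 as responses, T1 as covariate only.* The full effect is recovered, with slope on D near zero (-0.02 and -0.08 in the simulations).

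**Arm effect averaged over T1 to T3.** The expectation is (0 + d + d)/3 = 2d/3, with or without the covariate. With the covariate, the estimate was 0.6667 of the T2/T3 covariance-adjusted estimate in every simulated trial.

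**Power at d = 0.38, one-sided 0.05, 40 per arm.**

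| Analysis | rho 0.2 | rho 0.5 | rho 0.7 |
|---|---|---|---|
| T2/T3 mean, adjusted for T1 | 0.73 | 0.78 | 0.88 |
| T2/T3 mean, unadjusted | 0.71 | 0.62 | 0.58 |
| Change from T1 | 0.46 | 0.62 | 0.81 |
| T1-T3 average, no covariate | 0.51 | 0.40 | 0.35 |
| T1-T3 average, T1 covariate | 0.73 | 0.78 | 0.88 |

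In the last row the estimate and its SE shrink by the same factor, so power is kept and only the estimate is too small.

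**Binary feeding style.** In one large simulated set (rho 0.5), the logistic GEE log odds ratio over T1-T3 was 0.64 of its T2/T3 value without the T1 covariate, and 0.85 with it. Two thirds is not exact there.

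**The case against.** The strongest reply is that no such model is written. The T1-T3 sentence has no main clause and may only give the measurement schedule; the models are merely to be considered; and a condensed article normally leaves model terms to the full plan. Covariates are said to enter post-experiment analyses. If only T2 and T3 are responses, or a T1-by-visit term is fitted, the double role does no harm: with that term the T2/T3 effects equal those of covariance adjustment. This stands as a limit. A reader might infer that the plan definitely puts T1 on both sides of the model; the text supports this only as the natural reading, strengthened by the contrast with growth, which is tested at T2 and T3 only.

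Other strong inferences also fail.

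- *H2 asks for an average over visits.* The phrase "higher average maternal responsiveness scores" stands beside an average delay in introducing solids, which is one age per infant, so it means a group mean. The power calculation does count visits ("with a one-tailed TAD p < 0.05 over three measures"), but for infant growth.
- *The double role cuts the effect by a third and costs power.* The cut comes from averaging over T1, whatever the covariate. The power loss of that average arises without the covariate.
- *No usable contrast remains.* The T2/T3 arm difference from the same model is only mildly off.
- *A later trial would be 2.25 times too large.* That is 1/(2/3)², and it holds only if someone takes a T1-T3 average for the follow-up effect. The article does not say so.

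What the reply does not answer is the stated rule itself, under which T1 is adjusted for only when a test flags it.

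**Conclusion.** The point holds in limited form. What is stated is the test-triggered use of the T1 outcome value; T1 as an additional response is the natural reading and no more. If that reading is followed for a continuous score, the covariate leaves change from T1 unadjusted, and the T2/T3 difference is off by D(1-rho)/3, or about 0.09 SD at rho 0.5 when the test triggers. Imbalance falls in either direction, so this is an error in the individual trial and not an average bias over all trials. An average over T1-T3, if used, understates the follow-up effect by a third in every trial.

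The sizes assume complete data, compound symmetry and an equal effect at T2 and T3. They are exact for linear models such as maternal responsiveness and approximate for binary feeding style. They do not apply to age at first solids, which is not a score repeated at T1-T3, so extending them to all three maternal outcomes would go too far. Even on the benign reading, with T2/T3 responses only, routine adjustment is better: power goes from 0.71 to 0.73 at rho 0.2 and from 0.62 to 0.78 at rho 0.5.

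**What to change.** State how T1 enters, once. For maternal outcomes measured at all three visits, take T2 and T3 as the only responses. Include arm, visit, arm-by-visit and the T1 value of the same outcome as a pre-specified covariate whatever the baseline comparison shows, and report the arm contrast at T2 and at T3. Alternatively, keep T1 as a response with one common mean for both arms and never also as a covariate. Treat age at first solids separately. The cost is a sentence or two in the analysis section. The T1 values are already collected, and under the assumptions above no power is lost.
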